# Study Synopsis

| Title of clinical trial |  | Geriatrics and traumatology co-managing fragility fractures: effectiveness and success of implementation in a single centre setting |
| --- | --- | --- |
| Protocol Short Title/Acronym |  | G-COMAN FRACTURES |
| Sponsor name |  | UZ Leuven |
| Principal Investigator |  | [name] |
| Medical condition or disease under investigation |  | Older fragility fracture patients |
| Purpose of clinical trial |  | 1) To evaluate the effectiveness of a nurse-led geriatric-traumato co-management program using outcome indicators  2) To evaluate the feasibility of a nurse-led geriatric-traumato co-management program  2.1 To evaluate the reach and fidelity  2.2 To evaluate implementation targets 2.3 To evaluate implementation determinants  3)To evaluate the process of implementation of a nurse-led geriatric-traumato co-management program  3.1 To evaluate the reach and fidelity  3.2 To evaluate process outcomes |
| Primary objective |  | 1) Effectiveness evaluation: To determine if geriatric co-management is superior in preventing in-hospital complications |
| Secondary objective (s) |  | 1) Effectiveness evaluation: To determine if geriatric co-management is superior on following outcome indicators:  - length of stay  - unplanned readmissions within 30 and 90 days  - mortality  - functional status  - nutritional status  - quality of life  - falls and new fracture rate  - Discharge to a higher care level  - secondary fracture prevention started  - Cost-benefit of G-COMAN program  2) feasibility and process evaluation: To evaluate if geriatric co-management was successful implemented on the traumato ward:  -2.1 & 3.1: reach of the program and fidelity towards the core components of the care model  - 2.2: implementation targets  - 2.3: implementation determinants  -3.2: process outcomes:  * time to start physiotherapy  * time to start dietary advice  * use and duration of physical restraints  * use and duration of indwelling catheters (urinary tract catheter or intravenous catheter)  * Medication reconciliation at admission and discharge  * referral to geriatric day clinic  * referral to fracture liaison services |
| Trial Design |  | pre-post implementation study on the traumatology ward of the University Hospitals Leuven. |
| Endpoints |  | In-hospital complications (primary endpoint)  Length of stay, unplanned readmissions, mortality, functional status, nutritional status, quality of life, falls and new fracture rate, discharge to a higher care level, secondary fracture prevention, cost-benefit (secondary endpoints) |
| Sample Size |  | Pre-post cohort: Al least 108 patients per group  Feasibility study: 15 patients and 30 health care professionals |
| Summary of eligibility criteria |  | Pre-post cohort: Hospitalised patients aged 75 or older with a fragility fracture on the traumatology ward (E456) of the University Hospitals Leuven  Feasibility study:  - Hospitalised patients aged 75 or older with a fragility fracture on the traumatology ward (E456) of the University Hospitals Leuven  - Health care professionals of E456 will be included if they had four or more weeks of ‘full time’ experience with the programme. |
| Maximum duration of treatment of a  Subject |  | Not applicable |
| Version and date of final protocol |  | Amendment 2: 22-04-2022 |
| Version and date of protocol amendments |  |  |

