### 3.3 Secondary endpoints

1) Effectiveness evaluation

The secondary endpoints include comparison between the two groups on **patient outcome**:

- Length of hospital stay

- quality of life: EQ-5D^10^ (at admission, discharge, 1 month, 3 months, 6 months and 12 months post-surgery)

- functional status: Parker Mobility Score^11^, modified Barthel Index^12^, Lawton and Brody Scale^13^, Katz index (admission, discharge, 1 months, 3 months and 6 months post-surgery).

- hospital readmissions (30 and 90 days after discharge)

- falls (= “an unexpected event in which the patients comes to rest on the ground, floor or lower level”) and new fractures, either by retrospectively checking electronic patient record for any contact after discharge to any hospital or emergency department stating the occurrence of falls or new fractures) and by a questionnaire send out to patient and care givers. (admission, in-hospital, at discharge, at 1, 3, 6 months post-surgery 12 months post-surgery)

- Living situation: defined in 5 categories: living alone at home, living with spouse/partner, living with children, assisted living, living in a facility with 24h care such as nursing home). Details of care provided will be recorded as one of the following categories: 24h care, daily, irregular, no care. (admission, discharge, 1 month, 3 months post-surgery, 12 months after surgery)

- mortality (in-hospital, 1 month post-discharge and 12 months after discharge)

- secondary fracture prevention: documentation of fall risk assessment, medication review of calcium/vitamin D use and osteoporosis treatment, appointment to fracture liaison service (12 months after surgery)

- nutritional status: Mini Nutritional Assessment (MNA) ^14^ (at admission, 1 month, 3 months and 6 months post-surgery)

- cost-benefit analysis:

Costs will be assessed using a model that registers key hospital activities from the electronic patient record (KWS): 'beeldvorming', 'daghospitalisatie', 'dialyse', 'functiemeting', 'hospitalisatie', 'hospitalisatie ITE', 'labo', 'operatiekwartier', 'paramedische staf', 'raadpleging', 'raadpleging functiemeting', 'radiotherapie', 'spoedgevallen'. The model was developed by UHL.

2. Feasibility evaluation (is the intervention successfully implemented?):

2.1:

- the reach of the program (% of all eligible patients that were included in the G-COMAN program, defined as the patients who completed the questionnaire)

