### 4.2 Exclusion criteria

- patient in palliative care setting not expected to live longer than 3 months.

- multi-trauma injuries except for presence of multiple vertebral fractures

- patient or assigned representative are unable to speak and/or understand Dutch

- periprosthetic fracture

- concomitant joint-infection

- admission from another hospital or hospital unit (reason: no full baseline data on premorbid conditions such as mobility, functional status, … available)

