# Trial Procedures

### 5.1 By visit

### Baseline assessment

All patients who were screened for the inclusion and exclusion criteria will be entered on the ‘Subject screening log’ (see appendix 1). **Demographical data** (gender, age, height and weight (to calculate the Body Mass Index), date of admission and living situation), American Society of Anaesthesiologists (ASA) physical status class^15^, comorbidities (age adjusted charlson comorbidity Index (ACCI) will be all collected by reviewing the patients’ medical record. **Functionality** (Parker Mobility Score, modified Barthel Index, Lawton and Brody Scale, Katz index), **quality of life** (EQ-5D), **fall history and residential status** will be assessed referring to the patient’s pre-injury status. **Mental status**, based on cognition, and **nutritional status** will be assessed with respectively Mini-cog and mini nutritional assessment. Details relative to the **injury** (side affected, fracture location, fracture classification), **surgery** (time to surgery, type of procedure), and total number and intake of relevant **medication** will be documented as well. All variables, except for the quality of life, can be retrospectively collected using the electronic patient record.

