### At discharge

The research assistant will monitor the incidence of complications using patient assessment (4AT) and by monitoring the patients record throughout hospitalization, and will assess the outcomes on hospital discharge using patient interview. **Discharge date, medication and mortality** will be evaluated based on the electronic patient record. **Functional status** is measured using the Parker Mobility Score^11^, Barthel Index ^12^, Katz index and Lawton and Brody scale based on reports, if possible from the patient, from next of kin or from nursing staff. **Quality of life** will be evaluated using the EQ-5D questionnaire. **Fall history** will be evaluated using a questionnaire. **Cognition** will be assessed using the Mini-cog test. **Living situation** will be defined within the next 5 categories: living alone at their own home, living with a spouse/partner at their own home, living with children or sibling, living in assisted living facility, living in a facility with 24u care (nursing home, rehabilitation setting,…). Details of care provided will be recorded as one of the following categories: 24h care, daily, irregular, no care. Variables that can be retrospectively collected are as follows: discharge date, medication, mortality, fall history and living situation.

Also **several process outcomes** of the G-COMAN program will be evaluated using registrations in the electronic patient records and by patient interviews: reach of the program (% of eligible patients that were effectively enrolled into the program), fidelity to the program (% of patients included in G-COMAN traumatology program who had a screening or assessment focusing on *delirium, nutritional status, pressure ulcer risk* using a validated tool within 48h of admission to traumatology ward) and specific care process; such as the *time to start physiotherapy*; *time to start dietary advice*; use, *type and duration of fixation;* *use, duration and reason of indwelling catheters (urinary tract catheter or intravenous catheter); medication reconciliation; referral to geriatric day clinic* for follow-up; *and referral to a fracture liaison service (Zoledronate infusion or metabolic bone consultation).*

*Cost-benefit will be calculated by UHL financial division using the UHL cost model based on retrospective data collected at least 3 months post-discharge.*

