### 8.2 Analysis

Pre- and post-cohort: Categorical data will be expressed as numbers and percentages. Continuous data will be expressed as means with standard deviations. Baseline characteristics will be described and compared between usual care and intervention group to evaluate the baseline equivalence. If equivalent we will test the absolute difference for our primary outcome ‘in-hospital complications’ between the two groups (t-test). If not equivalent, we will test the mean number of in-hospital complications in both groups.

Non-parametric tests will be used to compare baseline characteristics between patients who are losted to follow-up from the control and intervention group. A missing data analysis (multiple imputation) will be performed for baseline characteristics.

In addition, univariable and multivariable regression models will be used whereby the outcome will be the number of in-hospital complications. Following baseline characteristics will be used to control for potential baseline confounding: age, gender, functional status pre-fracture (Katz ADL), physical performance (Parker Mobility score pre-fracture, grip strength), cognitive status (Mini-Cog), multimorbidity (Charlson Comorbidity Index) and nutritional status (Mini Nutritional Assessment).

Secondary analyses will consist of univariable statistical tests (chi^2^ or Fisher’s exact test for categorical variables; t-test or Wilcoxon rank-sum test for continuous variables) to evaluate differences between the two treatment groups. Logistic regression will be used for dichotomous outcomes, survival analyses for time to event variables (with mortality defined as a competing risk for the outcome readmission), and ANCOVA for mean inter-group differences

Longitudinal data will be analyzed by means of mixed effects regression models to estimate differences in mean scores (eg. EQ-5D, modified Barthel Index, Parker Mobility Score, Lawton and Brody Scale) between follow-up and the respective baseline assessment by treatment group. Statistical significance is established at p-value < 0.05.

Enrolled patients who withdraw from the study follow-up for any reason (withdrawal of consent, death, loss of follow-up, …) will be included in the analyses until time at which they withdrew.

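### Discharge to a higher care level has no event definition and no at-risk denominator, although eligible patients already in 24-hour care cannot have the event

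*Protocol*

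**What the plan says.** The endpoint appears only in the protocol's Study Synopsis: once among the secondary objectives as "Discharge to a higher care level", and again in the endpoint row as "discharge to a higher care level, secondary fracture prevention, cost-benefit (secondary endpoints".

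Section 3.3 has no endpoint of that name. It lists living situation in five categories, the last being "living in a facility with 24h care such as nursing home", and a separate four-level record of care received: "24h care, daily, irregular, no care". It does not say which scale defines a higher care level, or that the event is a change from before the fracture.

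The At discharge part of section 5.1 repeats the five categories but describes the last as "living in a facility with 24u care (nursing home, rehabilitation setting", so it adds rehabilitation settings that 3.3 does not mention.

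Eligibility (4.1, 4.2) sets no condition on residence. The nearest exclusion is "admission from another hospital or hospital unit", which does not cover nursing-home residents.

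On analysis, 8.2 says "Secondary analyses will consist of univariable statistical tests" (chi-square or Fisher for categorical variables) and that dichotomous outcomes get logistic regression. It names no covariates for that regression and no restricted patient set. The listed confounders belong to the model for the number of complications, and prior residence is not among them.

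The Baseline assessment part of 5.1 records "fall history and residential status" with reference to the pre-injury state. The flowchart in 3.6 shows living situation at admission and discharge for the retrospective controls as well.

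**The concern.** The endpoint is directional: a patient has to leave at a higher level of care than before. Someone who already lived in a 24-hour facility is at the ceiling of either recorded scale and counts as a non-event whatever the programme does. Such patients are eligible, so an all-patient comparison carries a block of certain non-events in each cohort.

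This has two consequences. First, the absolute effect is diluted and some power is lost. Second, the crude event rate depends on the proportion of residents in the cohort. The pre- and post-cohorts are not randomised, are recruited in different calendar periods (4.3), and the pre-cohort is part prospective and part retrospective (3.4). If their resident shares differ systematically, the difference shows up as a difference in discharge outcome.

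**Working it through.** **Plan's own figure.** The protocol gives no event rate, resident share or power for this endpoint. Its only sample-size figure, 108 per group (8.1), is for complications. It can be reproduced from 71% v 51% with continuity correction: 102 / 0.95 = 107.4, rounded up to 108. It is used here only for the number of evaluable patients: 108 x 0.95 = 102.6, about 103 per group.

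**Assumptions.** Resident share s of 10% to 35%. Event risk e among patients who can have the event: 30% to 50%. Residents have event risk 0.

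**Formula.** Crude rate over all patients = (1 - s) x e.

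**1. Dilution, equal shares in both cohorts.** Risk difference over all patients = (1 - s) x (e0 - e1). Risk ratio = (1 - s)e1 / (1 - s)e0 = e1 / e0, unchanged. Power is from the two-sided 5% normal approximation, with n = 103 for all patients and n = 103 x (1 - s) for patients at risk.

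| At-risk risks | s | Difference, all patients | Power, all | Power, at risk |
|---|---|---|---|---|
| 45% v 30% | 15% | 12.8 points | 0.50 | 0.54 |
| 45% v 30% | 25% | 11.3 points | 0.43 | 0.49 |
| 45% v 30% | 35% | 9.8 points | 0.37 | 0.43 |
| 50% v 30% | 10% | 18 points | 0.77 | 0.80 |
| 50% v 30% | 20% | 16 points | 0.70 | 0.75 |
| 50% v 30% | 30% | 14 points | 0.61 | 0.69 |

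The true differences are 15 and 20 points. Restricting to patients at risk gains about 3 to 8 points of power despite the smaller number.

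**2. Systematic difference in share, no programme effect.** Spurious difference = e x (s_post - s_pre). With s = 20% (pre) v 30% (post):

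- e = 30%: 24% v 21%, 3 points
- e = 40%: 32% v 28%, 4 points
- e = 50%: 40% v 35%, 5 points

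Here the risk ratio is distorted too: 0.70 / 0.80 = 0.875. With 103 per group, the all-patient test rejects about 8%, 10% and 12% of the time in these three cases instead of 5%. At 15% v 30% the figures are about 12%, 15% and 20%. The analysis of patients at risk stays at about 5%.

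**3. Chance difference in share only.** With a true share of 20% in both cohorts, the observed shares differ by up to 1.96 x sqrt(2 x 0.20 x 0.80 / 103) = 0.109 in 95% of studies. At e = 50% that moves the single estimate by about 0.109 x 0.5 = 5 points. The rejection rate of the all-patient test stays at about 5% (simulated 5.0% to 5.3%), because the test's variance already covers this.

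**The case against.** A reader might infer that the protocol prescribes a comparison over all patients. It does not. No denominator is written for any secondary endpoint, and an analysis plan that is not at hand may set one. That stands, so the point is that the protocol leaves the denominator open. What keeps it a protocol matter is that the endpoint itself is undefined: who can have the event is part of its definition, 3.3 replaces it with a descriptive variable, and 3.3 and 5.1 disagree on the top category.

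A reader might also infer that no planned model could adjust for residence. The confounder list is written for the complications model, and the logistic model for dichotomous outcomes has no stated covariates, so the omission of residence from that list proves nothing about this endpoint. The planned baseline comparison could also reveal an imbalance, but 8.2 attaches no consequence to it for this endpoint.

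A third tempting reading is that a chance difference in nursing-home share creates false positives. Step 3 shows that it does not raise type I error. Only a systematic difference does, and nothing in the protocol shows that one exists: both cohorts come from the same ward under the same criteria. Section 8.2 does itself warn of unbalanced variables in a non-randomised design.

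Finally, an all-patient risk difference is a legitimate quantity for a ward-wide programme, and the study was not sized for this endpoint. Both are true, and they are reasons to keep the all-patient result as a supplement.

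**Conclusion.** The point holds as a gap in endpoint definition with a modest but avoidable cost. Patients in 24-hour care are eligible and cannot have the event as long as care level is read from the recorded scales. The protocol fixes neither the event, nor the set of patients at risk, nor an adjustment for prior residence. Over all patients, the risk difference shrinks by (1 - resident share) and about 3 to 8 points of power are lost, with the risk ratio intact when shares are equal. A systematic 10-point difference in share (20% v 30%) gives a false benefit of 3 to 5 points at event risks of 30% to 50%. Every share and risk here is assumed, so these figures show sensitivity and are not estimates for this trial. It is a secondary endpoint, and the correction is worth making because it is cheap.

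**What to change.** In 3.3 and 8.2:

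- Define the event as a change from pre-fracture to discharge. State whether it uses the living-situation categories, the care categories or both, and how the categories are ordered.
- Make patients not in 24-hour care before the fracture the main analysis set for this endpoint, applied identically to the prospective pre-cohort, the retrospective pre-cohort and the post-cohort. Report the number of residents excluded per cohort.
- Within that set, adjust the logistic model for pre-fracture living situation. Restriction should come first, because a category with no possible events cannot be fitted sensibly as a covariate level.
- State how in-hospital deaths are counted.
- Reconcile 3.3 with the At discharge text in 5.1 on whether a rehabilitation setting belongs to the 24-hour care category, since this decides whether a rehabilitation discharge is an event.

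The change takes a few sentences. Living situation at admission and discharge is already recorded in all cohorts; if the care categories are also used, confirm that the retrospective records hold them. The cost is a smaller denominator and a result that applies only to patients not yet in 24-hour care. The all-patient comparison can stay as a supplementary analysis.

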# Background and rationale

Osteoporosis is the most common musculoskeletal disease and predisposes to fractures of hip, spine, proximal humerus, pelvis and wrist. Approximately around 80.000 fragility fractures occurred in Belgium in 2010 – with associated costs estimated at 606 million euros ^1^. Based on demographic forecasts it is predicted that by 2050 the number of hip fractures will have more than doubled from 2015^2^. These fragility fractures are **associated with pain, disability, need for institutionalization and even death** ^3^. The complex needs of the older fracture patient with multimorbidity, polypharmacy and geriatric syndromes require a holistic, multidisciplinary approach ^4^. This is the expertise of geriatricians and geriatric teams.

At the moment there is little cooperation between geriatricians and surgeons in Belgium due to the current care organization with silo financing. Moreover effects of geriatric consultation teams (as installed by Royal Decree in 2007, update in 2014) are quite limited as repeatedly observed in literature, due to their reactive nature and lack of implementation of advice given^5^. Hence, focus in literature has shifted to different forms of collaboration, such as **co-management with proactive care and shared responsibility** between geriatric and non-geriatric team members. This co)management model can have a significant impact on hospital stay, in-hospital complications and mortality^6^. Based on this convincing data the National Health Service (UK) has **incorporated geriatric care into its guidelines** and hospital reimbursement policy (Best Practice Tariff) resulting in a spectacular nationwide reduction in mortality of hip fracture patients^7^.

Some years ago, we successfully introduced a geriatric co-management model on the cardiology department in our hospital (G-COACH) with significant and clinical relevant results; a reduction in functional deterioration by 18%, better functional status at hospital discharge (Katz ADL 8.9 vs 9.5 in usual care), 13% less delirium and significant fewer nosocomial infections^8^.

Combining the successful results of G-COACH and the orthogeriatric care model abroad, we set up a care strategic project (2021-2024) for geriatric-surgical co-management within the University Hospitals Leuven, named **G-COMAN**. G-COMAN aims to optimize geriatric care in elderly surgical patients through a phased implementation of geriatric surgical co-management on the services traumatology, abdominal surgery and vascular surgery. This year (2021) is dedicated to pre-implementation. From 2022 onwards, G-COMAN will start implementing the program on the traumatology ward. Dedicated nurses will perform comprehensive geriatric assessments (CGA) in all patients aged 75 and older on the traumatology ward. By systematically organizing proactive care with collaboration and shared decision making between geriatric and surgical departments, postoperative care outcomes will hopefully improve.

This observational study will evaluate the **effectiveness of geriatric-traumatology** part of the G-COMAN program and will examine **which factors contribute to** a (non)successful **implementation** of the program as we aim to sustainable embed geriatric care aspects in the standard care of surgical services.

